| **SECTION B DETAILS OF THE PROJECT** | | |

| \| **B1** \| \| --- \| | **Please provide a brief summary of the project in simple lay person’s prose outlining the intended value of the project, giving necessary scientific background.**  *(max 500 words)***.**  **Notes**   1. This study extends our recently completed study on transcutaneous vagus nerve stimulation and compassion (The effects of vagus nerve stimulation on compassionate mind training and threat processing; UCL ethics ID: 4277/001). The details below outline how this study extends that work. 2. Testing during any COVID restrictions will strictly follow SLMS GSOP relating to personal contact during the pandemic.   **Background**  This study investigates whether a form of self-affiliation, namely, **self-compassion**, can be modulated using **non-invasive stimulation** of the vagus nerve (**transcutaneous vagus nerve stimulation; tVNS**) via **the external ear** (i.e. earlobe or tragus). The vagus nerve is part of the parasympathetic nervous system (the ‘rest and digest’ system; Murray et al., 2016) and its fibres are spread throughout the upper body, face and neck, including branches that innervate parts of the external ear, close to the skin. Recent research has shown that the vagus nerve is involved in a range of psychological processes including memory, threat/fear processing and positive affect (Kirby et al, 2017; Burger et al. 2016). For example, vagus nerve activity increases after compassionate mental imagery (Kirby et al., 2017). This activity can be assessed non-invasively using an ECG device that measures changes in heart rate (heart rate variability; HRV), which is an index of parasympathetic nervous system functioning.  Previous research has examined the effects of inducing compassionate feelings and then measuring vagus nerve activity (by measuring HRV). However, no published study has demonstrated the association between vagal activity and compassion by modulating the vagus nerve itself. Such studies not only have theoretical implications, but are also potentially valuable in the future development of interventions that employ tVNS or similar technology to augment psychological treatments incorporating compassion-focused techniques (e.g. compassionate mind training; compassion focused cognitive therapy).  In this study, we aim to *directly* test the relationship between vagus nerve activity and compassionate feelings using non-invasive stimulation of the vagus nerve in healthy volunteers. Our own recently completed unpublished related study (Title: The effects of vagus nerve stimulation on compassionate mind training and threat processing; UCL ethics ID: 4277/001) attempted to do this by **comparing** the effects of **active tVNS** **combined with compassionate mental imagery** with **‘sham’ tVNS** **combined with compassionate imagery**. However, that study only used two relatively brief tVNS sessions (only one of which was ‘active’) and evidence of vagal nerve modulation was weak. According to recent research (Yap et al., 2020), our stimulation protocol may have been insufficient to generate behavioural (including subjective) changes. In addition, that study included a compassionate imagery exercise in both the active and sham tVNS conditions, thus preventing us from examining the effects of imagery in isolation.  Our **primary research questions** are therefore:  ***(1)*** Is the tVNS protocol used here (7 stimulation sessions instead of 2, as used in our previous study) associated with reliable physiological (e.g. HRV) changes between lab Sessions 1 and 2?  ***(2)*** Is tVNS sufficient to **generate** compassionate subjective states; are these effects cumulative?  ***(3)*** Does tVNS **augment** the response to compassionate mental imagery compared to control imagery?  Because we are interested in the **interaction between stimulation and the mental imagery task**, we will use a **four group factorial design** in which participants are randomly assigned to **(i) tVNS + control imagery**, **(ii)** **tVNS + compassionate imagery**, **(iii)** **sham-stimulation + control imagery** and **(iv) sham-stimulation + compassionate imagery**. This design will help us establish whether tVNS alone generates compassionate behaviours/feelings and therefore allow us to directly link the effects of activity of the vagus nerve to compassionate feelings. Alternatively, the effects of tVNS on compassionate behaviour(feelings) may only be observed when combined with compassionate imagery (i.e. priming the vagus nerve may enhance the effects of compassionate imagery).  **Secondary questions** relate to:   1. The effects of tVNS and compassionate imagery on recognition of compassionate versus neutral emotional expressions 2. Moderation of effects by trait compassion, mindfulness and historical trauma (these are exploratory analyses intended for hypothesis generation, and will be declared as such in pre-registration documentation). |

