| --- | --- | --- |

| \| **B2** \| \| --- \| | **Briefly characterise in simple lay person’s prose the research protocol, type of procedure and/or research methodology (e.g. observational, survey research, experimental). Give details of any samples or measurements to be taken** *(max 500 words).*  **Design**  This is a randomised, controlled experimental study.  **Participants**  Participants will be healthy young volunteers.  **Screening**  Participants will respond to study advertisements which provide a link to study information and basic screening questions (age, sex, confirmation of absence of physical and mental health problems as well as the PHQ-2 and GAD-2 questionnaires to screen for severe anxiety or depression). Participants will provide contact information via the online screening and the researcher will email participants to arrange an additional telephone screening interview. The latter is essential for developing rapport with participants and ensuring proper understanding of the commitment required for the study. Eligible participants will attend two sessions at UCL and perform the between-session tasks on consecutive days.  **Lab Sessions 1 and 2 (1 week apart)**  Sessions 1 and 2 are identical except that additional instructions for ‘at-home’ stimulation are provided at the end of Session 1.  Upon arrival, participants attach the relevant physiological probes (see Appendix V) which will continuously record heart rate. They then complete a series of *trait* questionnaires that assess mood (using the DASS-21 questionnaire), mindfulness, compassion, attachment security and childhood trauma (see Appendix V for full list). They also complete the baseline (i.e. Timepoint 1; T1) emotion recognition task (with simultaneous eye-tracking; see Appendix V) and pre-stimulation *state* measures of self-compassion (SCCS) and positive and negative affect (PANAS; Appendix V).  The researcher then familiarises the participant with the tVNS device and attaches the ear-clip to the participant’s ear (tragus or earlobe, depending on stimulation condition; See Appendix V for further detail) before starting the stimulation threshold-setting procedure. The threshold is set individually for each participant and corresponds to the current level at which s/he experiences a mild tingling sensation. The experimenter will explain the device settings to the participant. Participants then detach the ear-clip, switch the Parasym device off, before reattach the ear-clip and switching the device on and ensuring that the stimulator produces the same sensation as before. This is required to ensure that participants can use the device independently for the at-home stimulations.  Thirty minutes of constant tVNS is applied while the participant relaxes and listens to a standard set of (neutral) music pieces. After this, the emotion recognition/eye tracking task and state questionnaires are repeated (post-stimulation; T2), followed immediately by either the self-compassion or ‘draw-a-face’ imagery tasks (depending on the participant’s random assignment to imagery condition; see below) while stimulation continues. They then complete the final emotion recognition/eye tracking task, state questionnaires (post-imagery; T3) and questions on mental imagery vividness (Appendix V).  Any non-disposable equipment that involves direct contact with the participant’s skin will be disinfected with >70% ethanol solution and placed in a UV-C chamber for 11 minutes before use with the subsequent participant.  At the end of Session 1 (day 1), the experimenter provides instructions on the use of the tVNS device to the participant, and ensures that they understand the importance of retaining the stimulation settings and site of stimulation. The device is very easy to use and verbal instructions will be supplemented with brief written instructions to ensure compliance with the procedure. In fact, the main instructions are to *not modify* the settings from Session 1, and simply attach the ear-clip and switch the device on for the required period, as previously instructed. Participants return for Session 2 (day 8) one week later and repeat the above procedure.  **Between session stimulation and imagery**  From day 2 (the day after Session 1) until day 7 (the day before Session 2), participants use the tVNS device independently. Prior to stimulation they will log on to the Qualtrics study site and complete the baseline state questionnaires on affect and self-compassion. They then either attach the ear-clip to the tragus or the earlobe (depending on randomised condition used in Session 1) and initially stimulate for 30 min. The Qualtrics page will display a visual countdown indicating the required duration of stimulation. To maximise cooperation and minimise disruption to participants, no specific concurrent task is prescribed during the 30 min stimulation, other than suggesting that the participant sits and relaxes/ watches a nature documentary (i.e. activities that are minimally arousing).  After 30 min, participants proceed to the compassionate or control imagery audio instructions (which are the same as those they received on Session 1, according to randomisation) which are played via the Qualtrics site. Participants are free to select the volume level and mode of listening, i.e. via earphones (as long as these do not interfere with the ear-clip) or through their device’s loudspeaker. State affect and self-compassion measures are repeated after stimulation and after the mental imagery task.  **Note**: the Parasym device is a small battery operated ‘straight-to-consumer’ device, **designed to be used at home** independently of additional researcher/clinician instruction (see accompanying product information or details at [https://www.parasym.co/parasym-device-transcutaneous-vagus-nerve-stimulation.html](https://www.parasym.co/)). |

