| --- | --- | --- |

| **SECTION C DETAILS OF PARTICIPANTS** |
| --- |

| \| **C1** \| \| --- \| | **Participants to be studied**   \| **C1a. Number of volunteers:** \| 140 \| \| --- \| --- \| \| Upper age limit: \| 35 \| \| Lower age limit: \| 18 \|   **C1b. Please justify the age range and sample size:**  Participants must be adults (hence the minimum age of 18). The upper limit will ensure that our sample is directly comparable to previous research in the field, including our recently completed study on tVNS (which used the same age range). In addition, ‘older’ women participants are more likely to experience hormonal changes (e.g. associated with menopause). Given that emotional processing can be affected by ovarian hormone levels, exclusion of older participants will reduce additional variability (noise) resulting from this. Clearly, ‘older’ men must also therefore be excluded to prevent imbalances in ages between sexes.  Sample Size: The sample size is based on pragmatic and statistical considerations. A sensitivity analysis suggests that n=140 will allow us to detect a between group effect size of d=0.48 (alpha=0.05; 1-beta=0.8; two tailed) for a critical comparison between active and sham tVNS groups on self-reported self-compassion (collapsed across imagery condition). This is a plausible effect size based on limited related research (e.g. d=0.6 in Petrocci et al, 2017, who examined the effects of anodal left temporal lobe transcranial Direct Current Stimulation on positive affect). We believe that tVNS’s effects on positive/affiliative mood states will be stronger than those found with tDCS (there is a stronger neurobiological rationale for tVNS), and as such, an effect size at least as large as observed by Petrocci et al (2017) can be expected in the current study. On this basis, an effect size d<0.5 is conservative, but seems appropriate given the uncertainties in the effects of tVNS on psychological functioning. Sensitivity analysis suggests that a lower sample size of n=120 is still sufficient to detect an effect size of 0.52. As such n=140 is aspirational and n=120 is acceptable. |
| --- | --- | --- | --- | --- | --- | --- | --- | --- |

| \| **C2** \| \| --- \| | **Accessing/Using Pre-Collected Data:**  **If you are using data or information held by a third party, please explain how you will obtain this. You should confirm that the information has been obtained in accordance with the General Data Protection Regulation 2018.**  NA |

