| \| **C8** \| \| --- \| | **Will any form of deception be used that raises ethical issues? If so, please explain.**  Although frank deception will not be used, it is necessary to conceal aspects of the study design and aims from participants because expectancy effects could invalidate the findings. In particular, participants are only informed that stimulation will be applied to the “outer ear” rather than the specific locations of stimulation (tragus or earlobe) to which they may be assigned. This is a *critical requirement* for the study, because if participants are told in advance that only one of two stimulation sites is expected to be ‘active’, they can easily obtain information about the active site and blinding would be removed. Interpretation of the findings would then be impossible as we would not be able to disentangle ‘real’ effects from expectancy-induced changes. As such participants will be ‘blind’ to the nature of the *active* stimulation.  On balance, given the need for incomplete disclosure of our aims and hypotheses, we believe it is necessary to include a statement on the use of deception in PIL. |
| --- | --- | --- |

| \| **C9** \| \| --- \| | **Will you provide a full debriefing at the end of the data collection phase?**  **Yes**  **No**  If ‘No’, please explain why below.  Full debriefing will occur at the end of session 2, including disclosure about the concealed aspects noted above. Participants will be requested not to discuss these debriefing details with others. |
| --- | --- | --- |

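### A week of unsupervised use of an identifiable consumer tVNS device leaves a route to unblinding, and the protocol text describes no check of allocation belief before debriefing

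*Protocol*

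**What the plan says.** **Blinding (C8).** Concealing the active site is called a critical requirement. Participants are told that stimulation goes to the outer ear "rather than the specific locations of stimulation (tragus or earlobe) to which they may be assigned". The reason given is conditional: if participants were told in advance that only one of two sites is expected to work, "they can easily obtain information about the active site and blinding would be removed", and the findings could not be interpreted.

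**Device and home use (B2).** In Session 1 the participant handles the device, which B2 names as Parasym, and is told to keep the same settings and site. From day 2 to day 7 they attach the clip to the tragus or earlobe themselves and stimulate for 30 minutes with no set task. They rate affect and self-compassion on Qualtrics before stimulation, after it and after imagery. The Note describes a consumer product meant for home use "independently of additional researcher/clinician instruction (see accompanying product information or details at" a public web address. For instructions, B2 says that participants receive verbal guidance and a brief written supplement.

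**Outcome the trial is sized on (C1b).** The sensitivity analysis is "for a critical comparison between active and sham tVNS groups on self-reported self-compassion (collapsed across imagery condition").

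**End of concealment (C9).** Full debriefing, including what was concealed, takes place at the end of Session 2. The last lab items that B2 lists are the T3 task and state questionnaires and questions on imagery vividness. It refers to Appendix V for details of the measures.

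**The concern.** The stated safeguard works before the study starts: it limits what participants are told. It does not cover what they can find out once they have the device. Each participant knows their own site from Session 1 and then has six days alone with an identifiable consumer product, often while logged on to a web page. A participant need not know that two sites are under test. A published picture of the clip on another part of the ear would be enough to raise doubt in an earlobe user and confidence in a tragus user.

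Bias by this route has a direction. It would raise active ratings, lower sham ratings, or both, and so favour tVNS. It would also begin only after Session 1. An arm difference in self-ratings that grows over the week is what B1's second research question looks for when it asks whether effects are cumulative, so the bias would look like the effect of interest.

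Belief about allocation can be collected cleanly only before the debrief. No later analysis can recover it.

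**Working it through.** **1. The plan's own figures.** Inputs from C1b are "alpha=0.05; 1-beta=0.8; two tailed", "n=140 will allow us to detect a between group effect size of d=0.48" and "a lower sample size of n=120 is still sufficient to detect an effect size of 0.52". B1 says that "participants are randomly assigned to" four groups and gives no ratio. Equal groups are assumed, so collapsing over imagery gives 70 v 70 or 60 v 60.

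Detectable d = (1.960 + 0.842) × √(2/n per group):

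- N=140: 2.802 × √(2/70) = 0.474; 0.477 with the t distribution. Power at d=0.48 is 0.805.
- N=120: 2.802 × √(2/60) = 0.511; 0.516 with the t distribution. Power at d=0.52 is 0.806.

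Both stated figures reproduce and are not in dispute.

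**2. Which measures are exposed.**

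| Measure | Relation to home use | Exposure |
|---|---|---|
| SCCS, PANAS in Session 1 (T1 to T3) | before it | none by this route |
| SCCS, PANAS at home, days 2 to 7 | during it | yes |
| SCCS, PANAS in Session 2; change from Session 1 | after it | yes |
| HRV, Session 1 to 2 | spans it | less: physiological |
| Emotion recognition with eye-tracking | both sessions | less: task measure |

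C1b does not say at which time point the critical comparison is made. The rejection rates in step 4 apply if it is a Session 2 rating.

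**3. Size of a possible bias (assumed inputs).** Let p be the share who look the device up and e the resulting shift in self-rating, in SD. The documents give neither. Take p = 0.2 to 0.4 and e = 0.3.

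- Only sham ratings fall: bias = p × e. 0.2 × 0.3 = 0.06; 0.4 × 0.3 = 0.12. Against d=0.48: 12.5% and 25%.
- Both arms shift, in opposite directions and equally: bias = 2 × p × e. 2 × 0.2 × 0.3 = 0.12; 2 × 0.4 × 0.3 = 0.24. Against d=0.48: 25% and 50%.

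**4. Effect on the test.** With no true effect, 70 per group and two-sided 5%, the noncentral t distribution gives these chances of a significant result:

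| Bias (SD) | Chance of p<0.05 |
|---|---|
| 0.06 | 6.4% |
| 0.12 | about 11% |
| 0.24 | about 29% |

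The result depends heavily on the inputs. A wider sham-only range (10% to 50% unblinded, shift 0.3 to 0.8 SD) gives a bias of 0.03 to 0.40 SD and a chance of about 5% to 65%.

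**The case against.** There is a good deal to say for the protocol.

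- **The product information.** A reader might infer from the Note that participants are handed the manufacturer's leaflet or web address. The text does not say so. The Note sits in an ethics application and most naturally points the committee to an attachment. What B2 gives participants is verbal and brief written study instructions. This stands. What remains is that the device is identifiable and has a public page.
- **The content of that page.** Nothing in the documents shows that it gives the clip position. This stands as an assumption.
- **C8 concedes nothing.** One might read C8 as admitting that blinding fails. Its statement applies to participants told that only one site is active, which these participants are not. This stands. Even so, C8 does treat the active site as easy to find.
- **Other protection.** The current is set for each participant to a mild tingling with no difference by site, and each keeps one site throughout. Sham users therefore feel stimulation and have no second site to compare. This helps against guessing from sensation, but not against looking the device up.
- **Belief never measured.** This too is a tempting reading, but B2 is a short lay summary and Appendix V is not shown. The text supports only that no such measure is described.
- **Magnitude.** Both p and e are invented, so no figure above is evidence that bias of that size will occur.

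**Conclusion.** The point holds in a limited form. Home use of an identifiable device leaves a route to unblinding that the stated safeguard does not close, and the text at hand describes no measure of allocation belief before the debrief. If the route operates, it biases home and Session 2 self-ratings, and the test of cumulative effects, towards tVNS.

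This rests on two assumptions: that some participants look the device up, and that public information shows where the clip goes. With the illustrative inputs the bias is 0.06 to 0.12 SD if only sham ratings move, and 0.12 to 0.24 SD if both arms move in opposite directions.

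A reader might go further and conclude that the whole trial is uninterpretable. The documents do not support that: Session 1 ratings precede home use, HRV and emotion recognition are less exposed, and the sample-size figures are sound. This is a cheap improvement to make before data collection.

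**What to change.** 1. Cover brand and model markings, and refer to the device generically in all participant materials.
2. Confirm that the study's own brief instructions are the only ones issued, and that they carry the needed safety and handling information.
3. At the end of Session 2, after the last ratings and before the debrief, add two or three Qualtrics items unless Appendix V already has them: whether the participant believes their stimulation was active and why, what benefit they expected, and whether they looked the device up.
4. Report the answers by arm. The reason given for the guess matters, because a guess made at the end may reflect felt benefit rather than a look-up.
5. Label any analysis that leaves out those who looked the device up as exploratory. It selects on a behaviour after randomisation that may differ by arm, and so can itself bias the comparison.

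**Cost:** opaque labels and about one minute per participant. The small downside is that safety and handling information must be carried in the study's own sheet.

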| \| **C5** \| \| --- \| | **Recruitment**  (i) Describe how potential participants will be identified:  Participants will respond to posts about the study. They will voluntarily respond by clicking on a web address which will direct them to study information or contact the researchers by phone to request information.  (ii) Describe how potential participants will be approached:  Participants will not be directly approached by researchers. They will learn about the study via posts on social media (e.g. Facebook); online experiment recruitment sites (e.g. Experimatch; Call for participants), UCL’s psychology participant pool; word-of-mouth; adverts on UCL notice boards; in-house participant mailing lists and flyers.  (iii) Describe how participants will be recruited:  Participants passing the online screening will provide their contact information to allow the telephone screening interview to be arranged. During the phone screening, researchers will provide more details about what is expected of participants and will answer any questions. The researcher will also confirm that participants meet the full eligibility criteria.  If the potential participant meets relevant criteria they will be invited to the first of two experimental sessions at UCL. At the start of Session 1 they will be given a printed copy of the information sheet and will be able to ask any outstanding questions about the study. They will then be asked for their signed consent. In consenting, all participants will be told that they can discontinue participation at any time without having to give a reason. |
| --- | --- | --- |

| \| **C6** \| \| --- \| | **Will the participants participate on a fully voluntary basis?**  **Yes**  **No**  **Will UCL students be involved as participants in the research project?**  **Yes**  **No**  *If yes, care must be taken to ensure that they are recruited in such a way that they do not feel any obligation  to a teacher or member of staff to participate.*  Participant will not be approached by the research team directly. The PI (the only member of staff on the research team who might be considered to be in a position of ‘power’) will have no role in recruiting participants.  **Please state how you will bring to the attention of the participants their right to withdraw from the study without penalty?**  This will be stated on both the information sheet and consent form and reiterated verbally at Session 1. |
| --- | --- | --- |

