**SECTIO**

| \| **D1** \| \| --- \| | **Will the research involve the collection and/or use of personal data?**  **Yes**  **No**  ***Personal data*** *is data which relates to a living individual who can be identified from that data OR from the data and other information that is either currently held, or will be held by the data controller (the researcher).*  *This includes:*   - *any expression of opinion about the individual and any intentions of the data controller or any other person toward the individual.* - *sensor, location or visual data which may reveal information that enables the identification of a face, address, etc (some postcodes cover only one property).* - *combinations of data which may reveal identifiable data, such as names, email/postal addresses, date of birth, ethnicity, descriptions of health diagnosis or conditions, computer IP address (if relating to a device with a single user).*   **If yes, is the research collecting or using special category data as defined by the GDPR 2018**, for example data:   - - which reveals racial or ethnic origin, political opinions, religious or philosophical beliefs, trade union membership ;   - data concerning health (the physical or mental health of a person, including the provision of health care services) ;   - data concerning sex life or sexual orientation ; or   - genetic or biometric data processed to uniquely identify a natural person. - **data which might be considered sensitive in some countries, cultures or contexts?**   **Note that if you intend to process ‘special category’ information you will need an ‘additional’ legal basis for processing that particular data and further safeguards will need to be put in place.**  **If yes, state whether explicit ethical informed consent will be sought for its use and what data management measures are in place to adequately manage and protect the data.**  Our intention to collect personal data is explicitly stated on the information sheet and we will seek consent for collecting this data in the consent form.  Data management: All data are collected and stored electronically at source (via Qualtrics or physiological devices). Paper-based consent forms will be scanned and stored digitally as soon as practical, at which point, paper copies of these forms will be shredded.  Eligible participants will be assigned a participant number and as such, the data will be pseudonymous until data collection is complete. At that point, names / contact details will be securely deleted and the data will be fully anonymised. If participants have indicated that they would like to be contacted in the future for related research (per the original consent form), only their name, email address and phone number will be retained. Any reference to participation in the current study (including participant number) will not be retained with contact details. This information will be stored in a password protected file on a secure online UCL server.  While in pseudonymous form, the data will be stored on password protected spreadsheet files on secure UCL server-based storage. Participant names/contact details will be stored separately on a *single* password protected spreadsheet. The latter will *not* be transferred via email and there should be no occasion for this file to be copied or stored on any portable device. Individual digital data files (e.g. from the psychophysiological tasks/devices) will be stored securely. |

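### Disclosing the stimulation sites at each participant's own Session 2 leaves the blinding of later participants resting on an unenforced request not to talk

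*Protocol*

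**What the plan says.** C8 explains what is hidden and why. Participants hear only that the outer ear will be stimulated, not which of the two locations is used. The stated reason is that, if they were told beforehand that just one site is expected to work, "they can easily obtain information about the active site and blinding would be removed". The protocol puts the consequence strongly: "Interpretation of the findings would then be impossible as we would not be able to disentangle ‘real’ effects from expectancy-induced changes".

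C9 then sets the timing of disclosure: "Full debriefing will occur at the end of session 2, including disclosure about the concealed aspects noted above". That is the end of each participant's own second visit (day 8), although the form question asks about debriefing at the end of the data collection phase. The next sentence adds a safeguard: "Participants will be requested not to discuss these debriefing details with others".

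C5(ii) lists the recruitment channels. Alongside social media and online recruitment sites they include "UCL’s psychology participant pool; word-of-mouth; adverts on UCL notice boards; in-house participant mailing lists and flyers".

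D1 keeps names and contact details until data collection is complete and then says: "At that point, names / contact details will be securely deleted".

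**The concern.** By C8's own account, a participant who knows which site is active before giving outcome data is no longer blind. Under C9 the number of people who hold that knowledge grows with every completed Session 2, and some of them belong to the same networks from which later participants come.

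Anyone who learns the active site also learns their own arm, because B2 has participants attach the clip to the tragus or earlobe themselves on days 2 to 7. The comparison that C1b calls critical is active versus sham on self-reported self-compassion, an outcome open to expectancy. The likely direction of bias is towards the hypothesis: informed active participants expect benefit and informed sham participants do not. Such a shift cannot be separated from a true effect afterwards unless someone has recorded who knew.

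**Working it through.** **Does disclosure overlap with recruitment?** The protocol gives no recruitment calendar, so this is an inference. C1b plans 140 participants and accepts 120. B2 gives each of them two laboratory visits a week apart. Unless all of them attend Session 1 within about a week, some will be debriefed before others start or finish. Staggered enrolment is very likely, but it is not stated.

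**The plan's own figure.** C1b gives a detectable difference of d=0.48 at n=140 (two-sided alpha 0.05, power 0.80). With equal groups of 70, which is my assumption, the normal approximation gives (1.960 + 0.842) × √(2/70) = 2.802 × 0.169 = 0.474. The noncentral t gives 0.477, and power at d=0.48 is 0.805. At n=120 the noncentral t gives 0.516 against the stated 0.52. Both figures reproduce, and this point does not dispute them.

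**Size of the bias.** The protocol gives neither a leak rate nor an expectancy effect, so both inputs are assumptions:

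- c = fraction of all participants who know the active site before giving outcome data, taken as equal in both arms
- e = active-minus-sham difference that expectancy produces among those participants, in SD units

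With no true effect, the expected difference is bias = c × e. The standard error is √(2/70) = 0.169 SD. The rejection rate is Φ(−1.960 + bias/SE) + Φ(−1.960 − bias/SE).

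Worked case, c=20% and e=0.5: bias = 0.20 × 0.5 = 0.10 SD; bias/SE = 0.10/0.169 = 0.59; rejection rate = Φ(−1.37) + Φ(−2.55) ≈ 0.09.

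| Informed (c) | Bias at e=0.5 | Type I error, n=140 |
|---|---|---|
| 5% | 0.025 SD | 5.2% |
| 10% | 0.05 SD | 6.0% |
| 20% | 0.10 SD | 9% |
| 40% | 0.20 SD | 22% |

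The result also depends on e. With 20% informed and n=140, the type I error is 6.4% at e=0.3 and 15.6% at e=0.8. At n=120 the inflation is slightly smaller because the standard error is larger: 8.4% with 20% informed and e=0.5.

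**Does deferral fit the rest of the plan?** D1 holds contact details until data collection is complete. An email sent after the last Session 2 and before deletion can therefore reach every participant.

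**The case against.** The best reply is that the protocol saw this risk and dealt with it. C8 is about being told in advance. C9 discloses only after a participant's last measurement, so that participant's blinding is intact, and participants are asked to keep the details to themselves. Prompt debriefing is a defensible ethical choice in a study that withholds information. Several channels in C5 reach people with no tie to earlier finishers, and no share of recruits by channel is given. All of this stands. It means that the leak may be small, and the table shows that at 5% to 10% informed the effect is close to negligible. The 40% row means 56 of 140 participants informed despite the request, and those who finish before any leak cannot be among them. The assumed 0.5 SD is itself slightly larger than the d=0.48 the trial is sized to detect.

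Three stronger readings are tempting, and the protocol does not support them:

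- A reader might infer that C8 and C9 contradict each other, or that the debrief undermines the blinding outright. Neither follows, because disclosure comes after each person's data and carries a confidentiality request.
- A reader might infer that the plan has no check on what participants believed. The procedure in B2 mentions none, but it refers to Appendix V for measures, and that appendix is not among the pages at hand.
- A reader might add that the home device is a named consumer product. That has nothing to do with debrief timing, and it is not part of this point.

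What remains is that a request nobody can enforce is the only safeguard shown for something the protocol calls critical, when a stronger one is available at little cost.

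**Conclusion.** The point holds as a residual, avoidable risk to the blinding of later participants. It is not an error in a figure, nor a conflict between sections. Its size cannot be known from the protocol. On the assumed 0.5 SD expectancy difference, the type I error at n=140 ranges from about 5.2% (5% informed) to 22% (40% informed). The conclusion rests on three assumptions: enrolment is staggered, knowledge is equally common in both arms, and expectancy favours the active site. The case for change is that the remedy is cheap and works only if adopted before debriefing begins, not that serious bias has been shown.

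**What to change.** 1. In C9, replace the full debrief at Session 2 with a partial one that leaves out which site is active and which is sham. Email that disclosure to all participants after the last participant's Session 2, and state in D1 that contact details are deleted only once it has been sent.
2. Unless Appendix V already has one, add a single Qualtrics item at the end of Session 2, before any debrief, asking which condition participants believe they had and whether they had heard about the study from someone else. Report the answers descriptively by arm. Do not use them to exclude anyone from the critical comparison: belief is recorded after randomisation, and a correct guess may result from a real effect, so exclusion could itself introduce bias.

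The cost is a change of ethics wording, one bulk email and one questionnaire item. The real downside is that participants wait longer for full disclosure, which the ethics committee would have to accept.
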